### Sample size

The sample size was calculated based on the primary hypothesis that KOKU combined with PC (IG1) will increase mean daily step count (first primary outcome) 6 months postoperatively, compared with usual care (CG). Based on previous observational studies, a mean daily step count of 5,000 ± 3,000 steps for the preoperative PA was assumed [79–83]. An increase of 1,500 steps per day in the IGs was assumed, which has been associated with an approximately 20% reduction in all-cause mortality risk among older adults [84, 85]. Under these assumptions, 64 participants per group are required to achieve a statistical power of 80% at a two-sided significance level of 5% using a *t*-test for independent samples. For the subordinated primary outcome (mean daily walking distance), which will be tested in a hierarchical order, a similar effect size is expected. Accounting for an anticipated dropout rate of 10%, the required sample size increases to 71 participants per group, resulting in a final total sample size of 213 participants.

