### Statistical analysis

For the first primary endpoint, the null hypothesis states that there is no difference in the mean daily step count at 6-months post-THA (T3) between IG1 and CG. The primary analysis will use linear regression at a two-sided significance level of 5%, adjusting for the stratification factor post-acute rehabilitation (outpatient, inpatient, or none) and preoperative mean daily step count. If this hypothesis is rejected, the subordinated primary endpoint (mean daily walking distance) at T3 between IG1 and CG will be tested (adjusted for post-acute rehabilitation and preoperative mean daily walking distance).

Subsequently, the following hypotheses will be tested hierarchically: IG2 (KOKU alone) vs. CG for mean daily step count at T3; IG2 vs. CG for mean daily walking distance at T3; IG1 vs. IG2 for mean daily step count at T3; and IG1 vs. IG2 for mean daily walking distance at T3. If any test in this sequence cannot be rejected, all subsequent tests will be considered exploratory only. This hierarchy reflects the assumption that IG1 (KOKU with PC) is at least as effective as, or superior to, IG2 (KOKU alone).

The primary analysis follows the intention-to-treat principle, with participants analyzed according to their randomized group. Intercurrent events are handled as follows: for non-compliance, additional interventions, AEs after randomization, new illnesses, or falls occurring between T2 and T3, a treatment-policy strategy (ICH E9 (R1)) will be applied, such that the estimated treatment effect includes the impact of these events. Death unrelated to the intervention will be handled under a hypothetical strategy, assuming the intervention does not affect the timing or occurrence of death within the observation window. If the T3 assessment cannot be performed due to a training-related injury or fatal event clearly attributable to the intervention, a “worst outcome” (step count = 0 steps/day, walking distance = 0 m/day) will be imputed as a composite strategy.

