Missing values for primary endpoints due to dropout or loss to follow-up will be imputed under a missing-at-random (MAR) assumption using multiple imputations with predictive mean matching. The imputation model includes the stratification factor (post-acute rehabilitation type) and mean daily step count / mean daily walking distance at T1 and T2 for first and subordinated primary endpoints, respectively. Relevant intercurrent events, and other important prognostic variables will also be incorporated.

To investigate the robustness of the results, sensitivity analyses will be conducted, including adjustments for further potential confounders such as age and comorbidity burden, as well as a reference-based approach (“copy reference”) to explore departures from MAR under a missing-not-at-random (MNAR) scenario. The reference-based approach assumes that participants in the IGs with missing data gradually converge toward the outcome trajectory of the CG.

A supplementary estimand will be used to quantify treatment effects under alternative strategies, including hypothetical strategies for non‑compliance and composite strategies (“worst outcome”) for cases in which the T3 assessment cannot be completed for intervention‑related reasons. A predefined subgroup analysis will compare participants with higher vs. lower preoperative PA, as those with higher baseline PA may derive less additional benefit from the interventions.

Secondary endpoints will be analyzed descriptively using appropriate summary statistics and confidence intervals. Safety analyses will summarize absolute and relative frequencies of postoperative complications from randomization onward.

All planned analyses will be described in detail in the Statistical Analysis Plan, which will be finalized prior to database closure and any conduct of unblinded analyses.

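### The one named subgroup analysis is framed as a higher-versus-lower split of preoperative activity; an interaction with the continuous step count would use the data better (minor)

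*Protocol article*

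**What the plan says.** The Statistical analysis section of the protocol article describes its only named subgroup analysis in one sentence: "A predefined subgroup analysis will compare participants with higher vs. lower preoperative PA, as those with higher baseline PA may derive less additional benefit". The reason given is effect modification. The sentence states no cut-point, does not name the activity measure to be split, and does not say whether or how an interaction with study arm is tested.

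Earlier in the same section, the primary linear regression for step count is described as "adjusting for the stratification factor post-acute rehabilitation (outpatient, inpatient, or none) and preoperative mean daily step count". Preoperative step count therefore enters that model with no categories mentioned. The Primary outcomes section defines it as a daily mean over valid sensor days, so it is a continuous quantity.

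The Sample size section gives the only figures on its distribution: "a mean daily step count of 5,000 ± 3,000 steps for the preoperative PA was assumed". The Statistical analysis section closes by leaving the detail of all analyses to a Statistical Analysis Plan, which is not shown.

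**The concern.** The question is whether the benefit of the interventions shrinks as preoperative activity rises. A two-class split treats everyone above the cut as alike and everyone below it as alike. If the benefit changes gradually, the split discards the variation within each class. It also ties the answer to a cut-point that has no stated basis.

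The trial is sized for a main effect, so power for effect modification is limited in any case. Losing part of it to the way the moderator is coded is avoidable, because the full-resolution variable is already in the primary model.

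**Working it through.** **The plan's own figure.** No figure is given for the subgroup analysis, so the sample size is checked first because it fixes the numbers available. Inputs from the Sample size section are a difference of 1,500 steps, SD 3,000 (d = 0.5), two-sided 5%, 80% power and a t-test. The noncentral t gives power 0.795 with 63 per group and 0.8015 with 64, so 64 reproduces. For 10% dropout, 64/0.9 = 71.1 and 64 × 1.1 = 70.4. The stated 71 per group and 3 × 71 = 213 agree within rounding.

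**Information kept by a split.** Suppose the treatment effect is linear in baseline steps X, and X is replaced in the interaction by the indicator I(X > c). The share of information kept is then the squared correlation between X and I(X > c). For a cut at the median it is

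(mean of X above the cut − mean of X below the cut)² / (4 × SD²).

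- *Normal X.* The two means differ by 2 × SD × √(2/π). The share kept is 2/π = 0.637, so 36% is lost.
- *Lognormal X with mean 5,000 and SD 3,000.* CV² = (3,000/5,000)² = 0.36, so σ² = ln(1.36) = 0.3075 and σ = 0.5545. The means differ by 2 × 5,000 × (2Φ(σ) − 1). The share kept is (2Φ(0.5545) − 1)²/0.36 = 0.49, so 51% is lost.

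The shape of the distribution is an assumption, because the article gives only a mean and an SD. A normal with those values would put about 5% of patients below zero steps (Φ(−5,000/3,000) ≈ 0.048), so some right skew is plausible.

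**Range over shapes and cut-points** (1,000,000 draws each, mean 5,000, SD 3,000):

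| Assumed shape | Lost, median cut | Equivalent increase in n | Lost, cut at mean | Lost, lower-quartile cut | Lost, upper-quartile cut |
|---|---|---|---|---|---|
| Uniform | 25% | 1.33 | 25% | 44% | 44% |
| Normal | 36% | 1.57 | 36% | 46% | 46% |
| Gamma | 43% | 1.74 | 39% | 63% | 36% |
| Lognormal | 51% | 2.03 | 44% | 71% | 40% |

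**Power.** This was simulated with 2,000 runs per setting. Assumptions were two arms of 64, an effect of 1,500 steps at the mean baseline, residual SD 3,000 × √0.75 (baseline–outcome correlation 0.5, also an assumption), and the continuous baseline kept as a covariate in both models. Ranges cover normal and gamma X.

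| Fall in effect per baseline SD | Continuous interaction | Median split |
|---|---|---|
| 750 steps | 35–37% | 22–27% |
| 1,000 steps | 54–58% | 35–40% |
| 1,500 steps | 87–88% | 67–69% |

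**The case against.** The strongest reply is that the article gives this analysis one sentence and defers detail to the Statistical Analysis Plan. A reader might infer that the trial splits the variable in place of testing an interaction. The text does not support that. It is silent on an interaction test, and its rationale shows that a difference in treatment effect is the target. An interaction, binary or continuous, may well be specified in the document not shown. The missing cut-point and model are ordinary deferrals and are not criticised here. What remains is the form that the article does state, a two-group comparison.

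A second reply is that the rationale need not mean a gradient; it fits a ceiling or threshold as well. This stands in part. The loss figures require roughly linear effect modification. Because a squared correlation is symmetric, a benefit that changed in one step exactly at the cut would make the linear term the less efficient choice. In the lognormal case much of the continuous term's advantage also comes from a few very active participants, where a ceiling would bend the line. The article claims no threshold, however, and gives no value for one.

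A third reply concerns consequences. A reader might infer that separate subgroup results will lead to a claim that the interventions work only in inactive patients. No separate within-subgroup significance tests are planned in the text, and naming a single subgroup with a stated direction already limits selective claims. Nor does the continuous test become reliable: at a fall of 1,000 steps per SD its power is still only 54–58%.

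**Conclusion.** The point holds in a limited form. The article frames its one named subgroup analysis as a two-class split of a measure that the primary regression already uses as a covariate. A continuous interaction would generally be more efficient and would not depend on a cut-point.

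For a median split under roughly linear effect modification, the loss is about 36% (normal) to 51% (lognormal, 5,000 ± 3,000) of the information on the interaction. In the simulated settings with a fall of 1,000 or 1,500 steps per SD, that costs about 18 to 21 percentage points of power. These figures are conditional on an unstated cut-point, an unstated distribution and linearity. Over the other shapes and cuts tabulated, the loss runs from 25% to 71%, and a true threshold effect would lose less. It would be wrong to quote a third to a half as a fixed property of the plan.

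The matter is minor. The analysis is supportive and lies outside the hierarchical tests, so the primary comparison, error control and sample size are untouched.

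**What to change.** State in the Statistical Analysis Plan that the main test of effect modification is an arm by T1 mean daily step count interaction, with step count continuous, added to the primary regression. Report the interaction estimate with its 95% CI. Also report the predicted IG1–CG and IG2–CG differences at chosen baseline values, for example 2,500, 5,000 and 7,500 steps. Keep the higher/lower split for display only, with the cut-point fixed in advance.

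The cost is the interaction term in an existing model; no new data or participants are needed. The downside is that linearity is assumed, which a spline can check. There is time for the change: 19 participants had been enrolled at submission, the last enrolment is planned for July 2027, and the Statistical Analysis Plan is to be finalised before database closure and any unblinded analysis.

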OPO	Usage data of the training app				X
Intervention acceptability					
OPO	Theoretical Framework of Acceptability Questionnaire				X
OPO	5-point Likert scale on global acceptability				X
Health-related resource use					
OPO	Questionnaire for Health-Related Resource Use in an Elderly Population	X			X
DV	Type of post-acute rehabilitation program		X		
DV	Participation in other aftercare programs		X		X
DV	Usage of another training app		X		X
Intervention delivery costs					
OPO	Personnel, material, and travel expenses			X	
Harms					
SA	Complications & adverse events		X	X	X

Abbreviations: *INT* Intervention, *pre-OP* Preoperatively, *post-OP* Postoperatively, *DV* Descriptive variable, *PO* Primary outcome, *SO* Secondary outcome, *OPO* Other predefined outcome, *SA* Safety outcomes, *WB* Walking bout, *UCLA* University of California, Los Angeles

^a^instrumented with the mTEST³ system [mHealth Technologies srl, Bologna, Italy] to measure spatiotemporal gait parameters (6-Minute Walk Test) and durations of sit-to-walk, walking, turning, and sitting segments (Timed Up and Go)

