### Harms and safety monitoring

Postoperative complications occurring between the preoperative baseline assessment (T1) and the 6-week postoperative assessment (T2) will be recorded at the on-site T2 visit.

Adverse events (AEs) will be documented for the period from the 6-week postoperative assessment (T2) to the 6-month assessment (T3), regardless of any causal relationship to the interventions.

These will be recorded by telephone interview conducted by the coaches at the end of the intervention period and at the very end of the on-site 6-month assessment (T3) by assessors. In addition to systematically collected postoperative and AEs at scheduled assessments, interim events spontaneously reported by participants (e.g., via telephone calls) will also be documented as reported.

The severity of complications and AEs will be classified into: (1) mild = transient and easily tolerated events, causing no or minimal interference with activities of daily living (ADLs) and not requiring medical intervention; (2) moderate = events causing noticeable interference with ADLs and/or requiring minimal or noninvasive medical intervention; (3) severe = events resulting in marked limitation of ADLs, requiring medical intervention or hospitalization, including life-threatening events and death.

An independent Data Safety Monitoring Board (DSMB) will oversee participant safety and trial conduct. The DSMB will consist of an orthopedic surgeon, a geriatrician, and a biometrician. It will regularly review accumulating reports of AEs, assess their causal relationship with the interventions and severity classification, and make recommendations on potential modifications or discontinuation of the study. The DSMB will operate under a written charter specifying its roles, responsibilities, and decision-making processes.

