### Randomization and blinding

After the 6-week postoperative assessment (T2), participants will be randomized to one of three study arms in a 1:1:1 allocation ratio using permuted block sizes, stratified by type of post-acute rehabilitation (outpatient, inpatient, or none). The random allocation sequence will be generated automatically using the web-based tool randomizer.at (Institute for Medical Informatics, Statistics and Documentation, Medical University of Graz, Austria; https://www.randomizer.at). Allocation concealment will be ensured through this centralized, Good Clinical Practice-compliant web-based tool. Randomization will be performed exclusively by authorized study personnel with individual access credentials.

All primary and secondary outcome assessments will be undertaken by assessors blinded to group allocation. Other prespecified outcomes, including training adherence and intervention acceptability, will be collected using self-completed questionnaires provided to participants after the final 6-month postoperative assessment (T3). These will be completed at home and returned to the study center by mail using prepaid envelopes.

Usage data of the KOKU app will be downloaded from the tablets of participant in the IGs by assessors only after completing of the on-site T3 assessment.

AEs will be documented by the unblinded coaches during the intervention period (for participants of both IGs) and at the end of the intervention period (for all participants). At T3, AEs will also be recorded by blinded assessors, but only at the end of the visit, after all other on-site assessments have been completed.

Processing of the DMOs after return of the IMU will be conducted at T3 by blinded study personnel who are not involved in the on-site T3 assessment.

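### The safety analysis names postoperative complications after randomisation, a class the harms section records for T1 to T2, and does not name the adverse events collected from T2 to T3

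*Protocol article*

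**What the plan says.** The Statistical analysis section of the protocol article gives the safety analysis one sentence: "Safety analyses will summarize absolute and relative frequencies of postoperative complications from randomization onward". It names no other class of safety event.

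The Harms and safety monitoring section describes two classes, each with its own period:

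- Complications: "Postoperative complications occurring between the preoperative baseline assessment (T1) and the 6-week postoperative assessment (T2) will be recorded at the on-site T2 visit".
- Adverse events: "Adverse events (AEs) will be documented for the period from the 6-week postoperative assessment (T2) to the 6-month assessment (T3"), whether or not they are causally related to the interventions.

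One three-grade severity scale serves both: "The severity of complications and AEs will be classified into" mild, moderate and severe.

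The Randomization and blinding section fixes the order of events: "After the 6-week postoperative assessment (T2), participants will be randomized to one of three study arms". For the time after randomisation it describes the collection of AEs only. The coaches' recording during the intervention is limited to the two intervention groups: "AEs will be documented by the unblinded coaches during the intervention period (for participants of both IGs"). The interview at the end of the intervention and the T3 visit cover all participants.

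Table 2 in the Outcomes section has a single safety row, "Complications & adverse events", marked at T2, during the intervention and at T3.

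**The concern.** The analysis sentence joins the label of one class to the time window of the other. Complications are the class recorded up to T2, before anyone is randomised. AEs are the class recorded once the interventions can have an effect, and no safety summary names them.

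The interventions include unsupervised home exercise in people aged 65 or over, starting about 8 weeks after hip replacement. The Statistical analysis section itself foresees that a training-related injury, or a death attributable to the intervention, could prevent the T3 assessment. Events of that kind are what a by-arm safety summary should show. An analysis plan that follows the sentence would inherit the mismatch, and one that reports AEs instead would depart from the published plan without explanation.

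**Working it through.** The plan gives no figure for safety, so there is none to reproduce. The check compares time windows, in weeks after surgery.

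**Inputs**

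- T1 = −1, T2 = 6 to 8, T3 = 26 ± 2 (Study design and setting).
- Complications recorded over T1 to T2, AEs over T2 to T3 (Harms and safety monitoring).
- Randomisation at R = T2 + g, with g ≥ 0 (Randomization and blinding). The documents do not give g. I assume 0 to 2 weeks, which puts R between weeks 6 and 10 and agrees with the stated intervention start at 8 ± 2 weeks.
- Analysis window: from R onward (Statistical analysis).

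**Step 1. Complications window against analysis window**

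Overlap = max(0, T2 − R) = max(0, T2 − (T2 + g)) = max(0, −g) = 0 for every g ≥ 0.

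- T2 = 6, g = 0: max(0, 6 − 6) = 0.
- T2 = 7, g = 1: max(0, 7 − 8) = 0.
- T2 = 8, g = 2: max(0, 8 − 10) = 0.

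The result does not depend on the assumed g.

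**Step 2. AE window against analysis window**

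Overlap = T3 − R.

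- T3 at week 26: longest 26 − 6 = 20 weeks, shortest 26 − 10 = 16 weeks.
- With the ± 2 weeks allowed for T3: longest 28 − 6 = 22 weeks, shortest 24 − 10 = 14 weeks.

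So the class that fills the analysis window is the one the sentence does not name.

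**Step 3. Are the two terms interchangeable in this document?**

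- The severity scale lists complications and AEs as two items.
- The description of collection after randomisation speaks of AEs only.
- The list of intercurrent events in the Statistical analysis section uses AEs for events after randomisation. The safety sentence, later in that section, switches to complications.
- The joint row in Table 2 fits complications at T2 and AEs afterwards. It does not say which class belongs to which time point, so it neither creates nor excludes a class of complications after T2.

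**Step 4. What each reading would count after randomisation**

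| Type of event | Strict reading | Everyday reading of postoperative complication |
|---|---|---|
| Late surgical complication | not counted | counted |
| Training-related injury without a fall | not counted | not counted |
| Other non-surgical AE | not counted | not counted |
| Fall, with any resulting injury | not in the safety summary, but in the fall calendars (secondary outcome) | same |

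**Step 5. Is ascertainment equal across arms?**

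| Source of AE reports | Intervention groups | Control group |
|---|---|---|
| Coaches, during the intervention | yes | no |
| Interview at the end of the intervention | yes | yes |
| T3 visit | yes | yes |

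A by-arm table that pools all sources would tend to show more AEs in the intervention groups even if the true rates were equal. Naming AEs is therefore necessary but does not by itself give a fair comparison.

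**The case against.** The strongest reply is that this is loose wording. The harms section says when complications are recorded; it does not say that a complication after T2 ceases to be one. Table 2 puts both classes in one row that extends to T3. The words about randomisation show which period is meant, and the data from that period are the AEs. A sensible analyst would tabulate them. This has force: the intention is probably to report AEs, and an empty safety table is unlikely in practice. It does not repair the text, because even the generous reading admits only surgical complications and leaves other AEs without a stated summary.

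A reader might also infer that the trial would report no safety comparison at all, or that falls, injuries and pain would go unreported. The documents do not support that. Falls are a secondary outcome, kept in weekly calendars after T2 that also record fall-related injuries. Hip pain and function are covered by the Oxford Hip Score. Secondary endpoints are to be summarised with confidence intervals. An independent DSMB reviews AE reports during the trial and assesses causality and severity. That is monitoring and does not replace a reported summary by arm, but it means that oversight of participants does not hang on this sentence.

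Finally, the article defers detail to the statistical analysis plan. Table layouts, and whether to tabulate causality, can properly wait for it. The point here is different: the article does state a class and a window, and the two do not fit together.

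**Conclusion.** The point stands as an inconsistency that should be fixed. As written, the class named in the safety analysis overlaps the analysis window by 0 weeks, whatever the interval between T2 and randomisation. The AE class, which covers about 16 to 20 weeks after randomisation (14 to 22 with the full T3 window), is not named. Those week counts rest on the assumed 0 to 2 weeks from T2 to randomisation; the zero overlap does not.

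The practical gap is narrower than a total loss of safety data. It consists of AEs after randomisation that are neither falls nor, on the generous reading, surgical complications. The documents give no expected AE rate, so the number of events affected cannot be estimated. No efficacy estimate, error rate or data collection is touched, which is why this is a should-fix point and not a more serious one.

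**What to change.** Replace the safety sentence in the Statistical analysis section, and carry the same wording into the statistical analysis plan:

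1. Adverse events from randomisation to T3, including any late surgical complications, are summarised by randomised arm as absolute and relative frequencies, by the three severity grades already defined.
2. Postoperative complications from T1 to T2 are summarised separately, as data from before randomisation.
3. The between-arm comparison uses the ascertainment common to all arms: the interview at the end of the intervention and the T3 visit. AEs that coaches record during the intervention in the two intervention groups are shown separately.

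The terms in the harms section, Table 2 and the analysis section should be aligned at the same time.

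The cost is a few sentences. The AEs, their severity grades and both common sources are already planned, so no new data collection is required. The article reports 19 participants enrolled at submission and last enrolment planned for July 2027, and the analysis plan is to be finalised before database closure and any unblinded analysis, so there is time to make the change.
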